## Abstract

**Background:**

Traumatic brain injury (TBI) is the leading cause of long-term disability in working age adults. Recent studies show that most acute TBI patients demonstrate vestibular features of dizziness and imbalance, often from combined peripheral and central vestibular dysfunction. Effective treatment for vestibular impairments post-TBI is important given its significant adverse impact upon quality of life and employment prospects. The most frequent peripheral vestibular disorder in acute TBI is benign paroxysmal positional vertigo (BPPV), affecting approximately half of acute cases. Although there is effective treatment for idiopathic BPPV, there are no high-quality clinical data for post-TBI BPPV regarding its prevalence, natural history, which treatment is most effective and when is the best time to treat. In particular, observational studies suggest post-TBI BPPV may be recurrent, indicating that hyperacute treatment of BPPV may be futile. Given the potential hurdles and the lack of accurate post-TBI BPPV data, the current study was designed to provide information regarding the feasibility and optimal design of future large-scale prospective treatment studies that would compare different interventions and their timing for post-TBI BPPV.

**Method:**

A multi-centre randomised mixed methods feasibility study design was employed. We aim to recruit approximately 75 acute TBI patients across a range of clinical severities, from three major trauma centres in London. Patients will be randomised to one of three treatment arms: (1) therapist-led manoeuvres, (2) patient-led exercises and (3) advice. Participants will be re-assessed by blinded outcome assessors at 4 and 12 weeks. Acceptability of the intervention will be obtained by patient interviews at the end of their treatment and therapist interviews at the end of the study. Primary outcomes relate to feasibility parameters including recruitment and retention rates, adverse events and intervention fidelity. We will also aim to provide a more accurate estimate of the prevalence of BPPV in TBI cases on the trauma ward.

**Discussion:**

The multi-centre nature of our feasibility study will inform the design of a future prospective treatment trial of BPPV in acute TBI. Important parameters we will obtain from this study, key for designing a future prospective treatment study, include estimating the prevalence of BPPV in TBI patients admitted to UK major trauma wards, and elucidating both patient and care-provider barriers in delivering BPPV treatment.

**Trial registration:**

ISRCTN, ISRCTN91943864. Registered on 10 February 2020.

## Background

Traumatic brain injury (TBI) is the most common cause of long-term disability in working age adults [1]. Indeed, in England and Wales, it is estimated TBI results in 1.4 million emergency visits per year [2], costing the economy £15 billion [3] and resulting in a significant impact on health-related quality of life for patients and carers [4]. Amongst the plethora of impairments experienced by TBI survivors, vestibular features or complaints of dizziness and/or imbalance are common, with large numbers of patients remaining symptomatic at 5-year follow-up [5].

The impact of dizziness on TBI survivors can be varied and burdensome, affecting physical, psychological and socioeconomic domains [6]. Acute and long-lasting dizziness can directly affect physical health, with implicit links to imbalance and therefore risk of falls [7, 8], which affect half of community-dwelling TBI survivors [9, 10]. The well-documented impact of falls on physical and psychological morbidity, mortality [11] and healthcare resource consumption [12] necessitates risk factors such as dizziness be appropriately managed. Imbalance and dizziness can also impair mental wellbeing, as demonstrated by studies describing direct links between the vestibular system and brain areas involved in emotional and cognitive processing [13–15]. Further, Chamelian et al. (2004) demonstrated dizziness to be an independent predictor of return to work, reporting only a third of dizzy patients had returned to work at 6 months compared to three quarters of patients without dizziness [16]. The implications of long-term unemployment not only include a socioeconomic burden for patients and their families, but also involve a wider impact on work productivity and costs for employers and society. Indeed, findings from a large observational study demonstrated the majority of patients with dizziness had reduced their workload and lost working days at just 3 months post onset of symptoms [17]. Therefore, the complex interplay between dizziness, physical health, neuropsychiatric function and socioeconomic factors provides the rationale for enhancing early diagnosis and treatment of dizziness.

The most frequently diagnosed cause of dizziness following TBI is benign paroxysmal positional vertigo (BPPV), theorised to be due to mechanical displacement of calcium carbonate ‘crystals’ or otoconia (Fig. 1) during the head injury itself [18]. As a result, patients typically, but not always, experience a sense of illusory self-motion when moving their head. Importantly, idiopathic BPPV is also associated with imbalance and falls [19] and hence, BPPV could exacerbate imbalance due to brain injury. Surprisingly, there is little evidence exploring falls in acute post-traumatic BPPV. Previous research in sub-acute TBI demonstrates the prevalence of post traumatic BPPV to range from 11 to 28% [20–22]; however, pilot data collected in acute TBI patients at St Mary’s Hospital, London, suggests it may be as high as 55% [23]. Further work is indicated to establish more accurate prevalence data. In particular, post-traumatic BPPV is thought to be more complex than the idiopathic form, with higher rates of multi-canal diagnoses and more treatment sessions required for resolution [21]. However, conflicting data exists regarding recurrence rates [21, 24].

**Fig. 1 Fig1:**
[figure not shown]
Schematic representation of displaced otoconia within the posterior semi-circular canal. Figure kindly provided by [name], April 2020

Robust clinical guidelines [25] direct the treatment of idiopathic BPPV, involving repositioning manoeuvres or repeated movements of the head and body to relocate the otoconia within the inner ear canals. However, there is a relative paucity of research regarding treatment of post traumatic BPPV, in particular regarding factors such as optimum dosage, or the most beneficial time to treat. The few studies which have examined treatment effectiveness were solely completed in sub-acute or chronic TBI patients and are further limited by their retrospective nature [21, 24], small sample size [20, 21] and lack of focus on BPPV resolution, symptom burden, or other patient-centred outcomes. The scarcity of acute prospective data noted may be a factor in the variability noted in routine assessment and treatment of post traumatic BPPV.

Indeed, despite the relatively high prevalence of post traumatic BPPV, emerging evidence suggests patients are not routinely assessed during the acute stages of their injury [26]. Our pilot work corroborates such data, indicating variable assessment and treatment of post traumatic BPPV appears to be complicated by two factors: (1) vestibular agnosia—impaired dizziness sensation which is also linked to imbalance via damage to the right temporal lobe circuits [27], and (2) clinician factors including insufficient training or skills. Vestibular agnosia may lead to a reduction in patients’ ability to report dizziness. This is clinically meaningful as patients with treatable diagnoses such as BPPV will not be assessed or treated if screening is solely based on symptoms. An initial report by Calzolari et al. [27] demonstrated vestibular agnosia leads to a seven fold reduction in clinician recognition of BPPV [27]. Furthermore, early results from a qualitative study exploring barriers to vestibular assessment and treatment at a major trauma centre in London demonstrated a variety of role and knowledge-based factors were linked with a lack of routine assessment and treatment of dizziness [28]. This is perhaps unsurprising given national head injury guidelines contain no reference to ‘vestibular’ or ‘dizziness’ assessments following head injury [2]. Therefore, the presence of vestibular agnosia and the lack of routine vestibular assessment and treatment may heighten the risk of clinically significant conditions such as post traumatic BPPV remaining undiagnosed, with patients predisposed to the acute and long-lasting sequelae of dizziness.

In summary, BPPV seems to affect the majority of acute TBI patients with possible long-lasting physical, psychosocial and economic consequences. Despite this, for a variety of reasons acute assessment and treatment is sub-optimal, whilst insufficient data exists to support decisions regarding effective treatment.

### Aim and objectives

The primary aim of this study is to evaluate the feasibility of conducting a future randomised controlled trial (RCT) investigating the effectiveness of treating BPPV in acute TBI.

Primary objectives focus on feasibility outcomes and will aid the design of a future definitive trial:
To establish trial recruitment rates, including the willingness of patients to be randomised to a treatment armTo determine trial retention rates, the fidelity of the intervention, its acceptability to participants and clinicians and any missing dataTo explore the incidence of adverse events

Secondary objectives will also support the design of a future RCT. They include:
An estimate of the prevalence of BPPV in acute TBICalculating effect sizes for primary and secondary outcome measures to thereby inform sample size estimates for future studiesExamining the relationship between vestibular perception, balance impairment and clinical outcome

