#### Interventions

Participants will be randomly allocated to one of three arms: (1) therapist-led repositioning manoeuvres, (2) patient-led exercises, or (3) advice.
*Therapist-led repositioning manoeuvres*

Repositioning manoeuvres are physical movements of the head and body typically used to treat idiopathic or traumatic BPPV [25]. Ward therapists will be taught to perform repositioning manoeuvres as per clinical guidelines [25]. Those diagnosed with BPPV affecting both left and right sides will be treated with the most symptomatic side first (or the side with the most intense nystagmus if the participant is not symptomatic). A repeat diagnostic test will be subsequently performed to determine the success of the intervention. The number of manoeuvres required for resolution of BPPV will vary between participants. If acceptable, the therapist will continue completing manoeuvres, up to a maximum of three manoeuvres per session, and a maximum of three sessions (over subsequent days where applicable). Participant discomfort, nausea, or vomiting would be indications to cease treatment. Any adverse events or reasons to stop the intervention will be recorded.
2.*Patient-led exercises*

Patient-led or Brandt-Daroff exercises are a form of physical self-treatment involving repeated movements of the head and trunk prescribed by clinicians as an alternative to, or in tandem with, repositioning manoeuvres. The National Institute of Clinical Evidence suggest Brandt-Daroff exercises as a treatment option for idiopathic BPPV [30], although their effectiveness is unknown post TBI.

Ward therapists will teach participants and carers (where required) the Brandt-Daroff exercises. A repeat diagnostic test will be completed. Following treatment, participants will be instructed to complete the exercises twice per day for 2 weeks, using a standardised, written exercise sheet. Participants will be asked to complete a home diary to record their adherence with the exercises.
3.*Advice*

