#### Sample size

As this is a feasibility study, no formal sample size calculation has been undertaken. However, Sim and Lewis [46] recommend at least 50 participants for this type of study. Accordingly, approximately 25 participants will be recruited into each arm, giving a total sample size of 75 patients. Our sample size compares favourably to previous trials investigating treatment of idiopathic BPPV [47, 48] and other feasibility studies [49, 50]. We will use secondary outcome measures to inform a sample size calculation for a future RCT.

A sample of up to ten patients who declined to take part in the study will be interviewed to examine their reasons for declining and therefore optimise recruitment strategies for a future study. Approximately ten therapists and 18 patients participating in the trial will also be interviewed at the end of the trial to explore intervention acceptability. Sample sizes for the qualitative component were drawn up following consultation of relevant guidance [51] which advocates an emphasis on sampling diversity as well as size in feasibility studies.

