#### Planned data analysis

Results will be reported descriptively to chart demographic and observational data. Participant recruitment/retention data will be reported using pilot and feasibility CONSORT guidelines [52]. An estimate of the prevalence of BPPV in acute TBI will be reported with 95% confidence intervals. The analysis will be undertaken on an ‘intention to treat’ basis, i.e. analysis will include all patients at the end of the study, whether or not they complete the intervention. We will assess the predictors of (i) return to work and (ii) BPPV at 3 months via a binary multiple logistic regression with predictors: DHI score, intervention group, duration of post traumatic amnesia and the presence of skull fracture. Our projected sample size of 75 patients should be sufficient to test these regression models given that each one has four variables. As there are two regression models, which both use the same predictor variables, the alpha will be adjusted (*α* = .025) based on the Bonferroni correction. We do not expect to demonstrate significant results from this data; rather, it will be used to calculate effect sizes for future prospective treatment studies.

Qualitative data will be transcribed verbatim and analysed using a Framework approach [53, 54]. This type of analysis uses a series of interconnected stages which enables the researcher to move back and forth across the data until a coherent account emerges. Following familiarisation with the transcripts, a framework is developed according to key issues or themes, into which data is then indexed. Data is then summarised by category and charted using the final coding index. Finally, key characteristics and differences between data are identified, allowing the generation of concepts, connections and relationships.

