#### Trial progression criteria

Trial progression criteria will be used to determine whether it is appropriate to move forwards to a RCT. Criteria include:
60% of those screened eligible for inclusion.Initially 30% of eligible patients are expected to consent to participate in the study, rising to 50% of those eligible consented as the research team gain confidence with consenting procedures.≤ 40% drop out rate.

Thresholds for participants consenting have been informed from previous feasibility studies in acute TBI [57, 58] and reflect some of the challenges of recruiting acute TBI patients [59].

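### Effect sizes observed with about 25 patients per arm are to inform the definitive trial's sample size, no other anchor is named, and for small to moderate effects they are too imprecise for that use

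*Protocol article*

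**What the plan says.** All places are in the protocol article.

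- *Aim and objectives* lists as a secondary objective the calculation of "effect sizes for primary and secondary outcome measures to thereby inform sample size estimates" for future studies.
- *Planned data analysis*, after the two logistic regression models, says the authors do not expect significant results and that "it will be used to calculate effect sizes for future prospective treatment studies".
- *Sample size* adds: "We will use secondary outcome measures to inform a sample size calculation for a future RCT".
- On numbers, *Sample size* states that "no formal sample size calculation has been undertaken" and that "approximately 25 participants will be recruited into each arm, giving a total sample size of 75 patients".
- *Trial progression criteria* accepts "≤ 40% drop out rate".

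No section gives a minimally important difference, an expected effect, a standard deviation or an event rate for any outcome. *Outcome measures* defines the primary outcomes as feasibility measures: eligible numbers, time to reach the recruitment target, drop-out, fidelity, completion of measures and adverse events.

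**The concern.** A trial of this size can estimate nuisance parameters tolerably well: standard deviations, a control event rate, retention. It estimates a difference between arms poorly. The required sample size varies with the inverse square of the target difference, so error in that difference is magnified. An observed effect that is too large by chance gives an underpowered RCT, and one that is too small gives a needlessly large RCT. Expecting no significant result already concedes that the comparison is imprecise, and the same imprecision limits the estimate as a design input.

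The objective also asks for effect sizes on primary outcomes. Those are feasibility measures, and a treatment effect on most of them cannot size an efficacy trial.

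**Working it through.** **Inputs from the protocol.** 25 per arm in three arms: 25 × 3 = 75, which reproduces the stated total. At the drop-out limit: 25 × 0.6 = 15 per arm, 45 in all.

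**Assumed, because the protocol gives no figure.** True SMD δ of 0.3, 0.4, 0.5 or 0.8; an RCT with two-sided alpha 0.05 and 80% power; one pairwise comparison.

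**Step 1: precision.** SE = √(2/n + δ²/(4n)).
- n = 25: SE is 0.284 at δ = 0.3 and 0.294 at δ = 0.8, so the 95% half-width is 0.56 to 0.58.
- n = 15: SE is 0.367 and 0.379, so the half-width is 0.72 to 0.74.

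For a binary outcome at an assumed 40% v 20%, the half-width is 1.96 × √(0.24/n + 0.16/n). The difference is then 20 ± 25 points (n = 25) or 20 ± 32 points (n = 15).

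The sentence in *Planned data analysis* follows logistic models, where the effect is a log odds ratio. At an assumed 50% v 30% the true value is ln(2.33) = 0.85. The unadjusted SE is 0.592 (n = 25) or 0.764 (n = 15), giving half-widths of 1.96 × 0.592 = 1.16 and 1.96 × 0.764 = 1.50.

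**Step 2: consequence if the observed effect d were used as the target.** Planned n per arm = 2 × (1.96 + 0.84)²/d². Treat d as normal with mean δ and the SE above.
- The plan is within half to double the required n when d lies between δ/√2 and δ√2.
- True power of the RCT is Φ(2.80 × δ/d − 1.96). It is below 60% when d exceeds δ × 2.80/(1.96 + 0.25), that is 1.266δ.
- No or reversed benefit means d ≤ 0.

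Worked for δ = 0.4, n = 25 (SE 0.286):
- Within half to double: Φ((0.566 − 0.4)/0.286) − Φ((0.283 − 0.4)/0.286) = 0.72 − 0.34 = 38%.
- Power under 60%: 1 − Φ((0.506 − 0.4)/0.286) = 35%.
- d ≤ 0: Φ(−0.4/0.286) = 8%.

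All shares below are of all feasibility trials, shown as 25 per arm / 15 per arm.

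| True SMD | Required n per arm | Within half to double | RCT power under 60% | No or reversed benefit |
|---|---|---|---|---|
| 0.3 | 175 | 29% / 23% | 39% / 41% | 15% / 21% |
| 0.4 | 98 | 38% / 30% | 35% / 39% | 8% / 14% |
| 0.5 | 63 | 46% / 37% | 32% / 36% | 4% / 9% |
| 0.8 | 25 | 66% / 54% | 23% / 29% | 0.3% / 1.8% |

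A simulation of 200,000 trials per scenario, with d drawn from the noncentral t distribution and corrected for small-sample bias, agrees closely. Its shares within half to double are 29%/23% at 0.3, 47%/37% at 0.5 and 67%/55% at 0.8.

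**Step 3: contrast with the standard deviation.** The 95% limits for a pooled SD, as multiples of the estimate, are 0.86 to 1.195 with 75 patients (72 df) and 0.825 to 1.271 with 45 (42 df). For a fixed target difference, n varies with SD². The resulting error in n is therefore 0.86² to 1.195² = 0.74 to 1.43 times, or 0.825² to 1.271² = 0.68 to 1.62 times. Both ranges stay within a factor of two.

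**The case against.** Several objections are sound and limit the point.

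- **Inform is not set.** A reader might infer that the observed estimate will be entered directly as the target difference. The protocol does not say so, and Step 2 models a rule it does not state. How estimates, intervals and an important difference would be combined may be in a fuller document. The sentence in *Sample size* fits taking SDs and event rates from the secondary outcomes, so it is weak support. *Aim and objectives* and *Planned data analysis*, however, both name effect sizes, and neither names another anchor.
- **Large effects.** A reader might infer that the error is as large as any plausible effect. That is not supported. The protocol gives no plausible range, and it describes treatment of idiopathic BPPV as effective. At SMD 0.8 with 25 per arm the half-width is 0.58. For an assumed 70% v 20%, the difference is 50 ± 24 points (25 per arm) or 50 ± 31 points (15 per arm).
- **Fifteen per arm** is the worst drop-out the progression criterion accepts, not a forecast.
- **Abandoning the RCT.** A reader might infer that a reversed effect would stop the programme. The progression criteria cover eligibility, consent and drop-out, with no efficacy threshold. *Study monitoring and data protection* mentions futility of a specific arm as a cessation criterion, but does not link it to these effect sizes.
- **The authors acknowledge low power**, and effect sizes are only one secondary objective. Both are true, but neither makes the estimate more precise.

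**Conclusion.** The point holds in a limited form. The protocol states that observed effect sizes will inform future sample sizes and names no other basis for the target difference. For a true SMD of 0.3 to 0.5, sizing on the observed effect would land within a factor of two of the required number in fewer than half of cases. At 0.8 it would still miss by more than that in about a third (25 per arm) to just under a half (15 per arm).

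These shares rest on the assumed SMDs, on 80% power at two-sided 0.05, and on the observed effect being used unmodified. The underpowering risk falls from 35–39% at SMD 0.4 to 23–29% at 0.8, so no single figure should be quoted alone. The feasibility aims themselves are unaffected. The fault lies in which quantity the trial is asked to supply, and it should be corrected.

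**What to change.** 1. Reword the objective in *Aim and objectives* and the matching sentence in *Planned data analysis*. For the RCT sample size, the trial should supply standard deviations, the advice-arm BPPV rate at 12 weeks and retention, each with a confidence interval.
2. State that the RCT's target difference will be a minimally important difference fixed in advance.
3. Report differences between arms with 95% confidence intervals, only to check that this difference is not ruled out.
4. Remove the word primary from the effect-size objective, since the primary outcomes are feasibility measures.

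Using an upper confidence limit for the SD in the RCT calculation is optional. It is one convention among several, and nothing in the protocol calls for it.

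The cost is wording. No extra patients, visits or data are needed. The real work is that the team must choose and justify a minimally important difference.

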## Methods

### Study design

Currently, it is not routine practice in all major trauma centres to assess for or treat BPPV in acute TBI. In order to implement any long-term changes to screening and/or treatment behaviours, it is necessary to identify any possible barriers to such changes in clinical practice. Therefore, a feasibility study utilising both quantitative and qualitative methods was deemed appropriate.

This multi-centre, mixed methods randomised feasibility trial will comprise a randomised trial with two intervention arms and one comparator arm, and a subsequent qualitative study (Fig. 2). Reporting of this protocol will comply with the SPIRIT statement.
Phase 1 will consist of a feasibility trial involving approximately 75 patients randomised to one of the three arms.Phase 2 will qualitatively explore the experiences of patients and clinicians participating in the trial and their views regarding progression to a randomised controlled trial. Patients who decline to take part will be invited for their feedback to enhance recruitment for a future trial.

